## Abstract

**Background:** It has been reported that maternal gestational environment may be programmed to have a significant impact on foetal and offspring health later in life. Studies have shown that children born to pre-eclamptic mothers are prone to obesity, hypertension, and diabetes in their adult life. However, such findings are yet to be established in an African population. This protocol is for a study aiming to investigate the relationship between pre-eclampsia (PE) and cardiovascular risk in children born to pre-eclamptic mothers in a South African population of African descents.

**Methods:** A prospective case-control design will be employed to recruit pre-eclamptic and normotensive pregnant women and their offspring after birth. Pregnant women will be assessed for cardiovascular risk factors including PE, obesity, haemodynamics, lipids, glycaemic indices, oxidative stress, and vascular function at 30 weeks of gestation. The cardiovascular risk profile of their offspring will be assessed at birth and 6 weeks later. The difference in cardiovascular risk profile between children born to the pre-eclamptic and normotensive mothers will be compared and the correlation between maternal and offspring cardiovascular risks will be investigated.

**Discussion:** This will be the first prospective study to assess the *in-utero* effect of cardiovascular risk in offspring born to pre-eclamptic women of African ancestry. It is expected that findings from this study will provide information on the cardiovascular effect of *in-utero* exposure to PE in a population of African ancestry. This knowledge will advise policy on the management of women with PE with a view of protecting cardiovascular health in offspring.

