### Study Design and Procedure

This will be a prospective case-control study involving babies born to pre-eclamptic pregnant women and babies born to normotensive mothers recruited at the Nelson Mandela Academic Hospital, Mthatha, Eastern Cape Province of South Africa. Pregnant women who meet the selection criteria will be recruited between weeks 20–26 of gestation and their cardiovascular risk profile assessed at week 30 of gestation. The cardiovascular risk profile of their offspring will be assessed at birth and 6 weeks later.

Recruited pregnant women will be assessed at baseline (week 30 of gestation) for cardiometabolic risk profile including their PE status, anthropometry, blood pressure, oxidative stress, and vascular function. The socio-demographic, obstetric, and medical history will be collected using a structured interviewer administered questionnaire. Their blood pressure (systolic and diastolic blood pressures (BP) and heart rate, and anthropometric measures including weight and height will be measured. A vicorder (SMT Medical GmbH&Co., Wuerzburg, Germany) will be used to measure pulse wave velocity (PWV) to assess arterial stiffness and ankle-branchial index (ABI). The retinal microvasculature via retinal imaging will be assessed for vascular changes using a Optomed Aurora retinal camera (Optomed, [name], Finland). Gestational ultrasound will be performed to determine placental morphometry, architecture and vascularization. Fasting blood will be collected for the assessment of lipid profile, glycaemic, oxidative stress, reno-cardiovascular, and endothelial function markers.

At birth, the gestational age and mode of delivery of the offspring will be noted. The Appearance, Pulse, Grimace, Activity, and Respiration (APGAR) score (1–5 min) will be determined. The weight, height/length and blood pressure of the child will be measured, and PWV measured using a vicorder. Cord blood will be collected for determination of cardiometabolic risk markers including lipid profile, oxidative stress, reno-cardiovascular and endothelial function markers. Six weeks after birth, blood pressure (BP) and anthropometric measurements and PWV assessment will be done in children. Then, blood and urine samples will be collected for the assessment of endothelial function, lipid profile, reno-cardiovascular and oxidative stress markers.

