### Data Collection

A standard interviewer administered structured questionnaire will be used to collect information on maternal health and cardiovascular risk factors at the beginning of the study (Supplementary file 1–Cardiovascular risk questionnaire). This information will include socio-demographics (sex, age, ethnicity, and location), socio-economic status (marital status, profession, income/revenue, and living standard), maternal obstetric history, family history, cardiometabolic health history, and cardiovascular risk factors (physical exercise, smoking, alcohol consumption, and feeding habit).

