### Physical Assessments

Anthropometric measurements will be done in accordance with the international standards guidelines (29). A wall-mounted Harpenden stadiometer will be used to measure participants height to the nearest 0.1 cm while weight will be measured using a wireless weight scale (Tanita body composition scale). In pregnant women, BP including the SBP, DBP, and heart rate will be measured after a 10 min of rest in the seated position using the Omron M HEM-907XL Professional Blood Pressure Monitor (Omron Healthcare, Kyoto, Japan) described by Muntner et al. (30) in triplicates at 3 min intervals. The oscillometric technique (Dinamap 8100) will be used for BP measurement according to the standard protocol for assessment of BP measurement in newborns by Nwankwo et al. (31). An ultrasound device will be used to assess the morphometry, architecture and vasculature of the placenta. This will include assessing the uterine, umbilical and middle cerebral arteries and uterine artery mean pulsating index determined. Foetal cerebroplacental ratio and anthropometry will be calculated when possible.

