### Statistical Analysis

STATA (Stata, College Station, Texas, USA) and IBM statistical package for social sciences (SPSS) Version 23.0 (IBM Corp). Armonk, NY, USA) will be used for data analyses. The Shapiro-Wilks test will be used to check for normality and data will be log-transformed and/or corrected for outliers when necessary. Descriptive statistics will be employed for data presentation as mean ± standard deviation (SD) or median ± interquartile range (IQR) for continuous variables and proportions (percentages) for categorical variables. Independent sample *t*-test will be used to compare mean differences between groups (pre-eclamptic and normotensive pregnant women and their offspring). Multivariate analysis using multiple analysis of variance (MANOVA) will be used to compare continuous variables for two or more independent variables where necessary. Chi-square test of association and Pearson correlation will be used to assess the relationship between cardiometabolic risk factors and PE at baseline and follow-up for both mother and child. A difference will be considered significant at α = 0.05.

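### Maternal obesity rests on weight and height at week 30, after pre-eclampsia has begun in cases and with no earlier weight named, so it is not a pre-exposure measure of adiposity

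*Protocol article*

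**What the plan says.** The Abstract lists obesity among the maternal risk factors and fixes the time: "Pregnant women will be assessed for cardiovascular risk factors including PE, obesity, haemodynamics, lipids, glycaemic indices, oxidative stress, and vascular function at 30 weeks". Study Design and Procedure repeats the timing and calls it baseline: "Recruited pregnant women will be assessed at baseline (week 30 of gestation) for cardiometabolic risk profile including their PE status, anthropometry, blood pressure". The same section names the measures: "anthropometric measures including weight and height will be measured". Physical Assessments gives a stadiometer for height and, for the rest, "weight will be measured using a wireless weight scale (Tanita body composition scale". It specifies no fat or body-water variable from that device.

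The women are in contact with the study earlier, since they "will be recruited between weeks 20–26 of gestation", but no weight is planned at that contact. Data Collection describes a questionnaire to "collect information on maternal health and cardiovascular risk factors at the beginning of the study". The items listed there do not include a pre-pregnancy or first-visit weight, and the questionnaire itself is a supplement that is not shown.

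The article gives no definition of maternal obesity: no BMI formula and no cut-off. The maternal data have two stated uses. Statistical Analysis will use *t*-tests to "compare mean differences between groups (pre-eclamptic and normotensive pregnant women and their offspring", and the Abstract says that "the correlation between maternal and offspring cardiovascular risks will be investigated".

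**The concern.** Body weight at 30 weeks includes the fetus, placenta, amniotic fluid and expanded plasma volume as well as the woman's own tissue. Weight and height at that time therefore mix adiposity with pregnancy gain.

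Timing relative to exposure adds to this. The Introduction defines pre-eclampsia as arising after 20 weeks, and Selection Criteria recruits women who are pre-eclamptic or normotensive at 20 to 26 weeks. A case is thus weighed with the disease already present. A variable that the exposure can alter is neither a pre-exposure risk factor nor a clean confounder.

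Maternal obesity is a plausible common cause of pre-eclampsia and of offspring cardiovascular risk, and the Discussion sets the study against obesity in South African children. If the variable carries part of the exposure, a case-control difference in it, or a correlation of it with infant markers, is hard to interpret. No later analysis plan can separate the components if only the week-30 weight was collected.

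**Working it through.** The documents give no maternal BMI, obesity prevalence, cut-off, weight gain or oedema weight, so there is no stated figure to reproduce. The check has a part that rests on the text and a part that is illustration.

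**Timing, from the text**
- Recruitment is at 20 to 26 weeks and weighing at week 30.
- The gap is 30 − 26 = 4 weeks to 30 − 20 = 10 weeks, with cases already classed as pre-eclamptic at the start of it.

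**Inflation of BMI (assumed height 1.60 m, assumed gain 6 to 12 kg)**
- Shift in BMI = gain / height², with 1.60² = 2.56.
- 6 / 2.56 = 2.3 kg/m² and 12 / 2.56 = 4.7 kg/m².
- With an assumed cut-off of 30, a woman whose pre-pregnancy BMI is 30 − 4.7 = 25.3 (gain of 12 kg) or 30 − 2.3 = 27.7 (gain of 6 kg) would reach it by week 30.

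**Share called obese (assumed normal BMI, cut-off 30)**
- Share = 1 − Φ((30 − mean − shift) / SD).
- The low end is a gain of 6 kg at 1.60 m (shift 2.34). The high end is 10 kg at 1.55 m (10 / 2.4025 = 4.16).

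| Assumed pre-pregnancy BMI | No shift | Shift 2.34 | Shift 4.16 |
|---|---|---|---|
| mean 26, SD 5 | 21% | 37% | 51% |
| mean 28, SD 6 | 37% | 52% | 64% |
| mean 30, SD 6 | 50% | 65% | 76% |

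**Difference between groups (assumed 1 to 4 kg more fluid in cases, nothing offsetting it)**
- Spurious difference d = 1 / 2.56 = 0.4 to 4 / 2.56 = 1.6 kg/m².
- Sample Size Calculation plans 61 women per group. At two-sided α = 0.05, the chance of a significant result in that direction is about Φ(d / (SD × √(2/61)) − 1.96).
- For 1 kg and SD 5: 5 × √(2/61) = 0.905; 0.391 / 0.905 = 0.43; Φ(0.43 − 1.96) = 6%.
- For 4 kg and SD 5: 1.5625 / 0.905 = 1.73; Φ(1.73 − 1.96) = 41%.
- With SD 6 the same two cases give 5.5% and 30%.
- With no shift, this chance is 2.5%.

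**Offset**
The Introduction links pre-eclampsia to babies small for gestational age and to placental malfunction. A smaller fetus and placenta lower case weight. The net shift is (extra fluid − fetal and placental deficit) / height². The documents give neither term, so its sign is open.

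**What a common shift does to the planned tests**
If every woman's BMI rose by the same amount c, the difference in means would be (m₁ + c) − (m₀ + c) = m₁ − m₀, and Pearson's r would not change. Only variation in gain, a difference between groups, or a cut-off can distort the results.

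**The case against.** The strongest reply is that both groups are weighed at the same gestational week and the planned *t*-tests and Pearson correlations treat measures as continuous. Inflation common to all women then leaves the mean difference and the correlation as they were. This stands. The larger figure above, 2.3 to 4.7 kg/m², matters only if obesity is dichotomised at a non-pregnant cut-off, and the article specifies no such variable.

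A reader might infer that obesity is over-called, and more so in cases. The documents do not support either statement as fact. The first needs a cut-off that the article does not give. The second rests on oedema, which the article never mentions, and on kilograms that are assumed, while small-for-gestational-age babies would pull the other way.

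It can also be said that the questionnaire supplement is not shown and may record an earlier weight, that the list of measures is not exhaustive, and that the first objective is to assess maternal risk during pregnancy. The supplement could indeed settle the matter, and an unseen item should not be called absent. But the article fixes obesity assessment at week 30 and names no other weight, so the plan as written yields the contaminated measure.

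Finally, the article plans no adjustment for obesity; the only confounder it names is drugs taken in pregnancy. Bias through adjustment is therefore conditional on a later decision to adjust.

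**Conclusion.** The point holds as a limited measurement weakness. Maternal obesity, as the article plans it, comes from a weight that includes gestational gain and is taken after pre-eclampsia has begun in cases. It would probably over-classify obesity under a non-pregnant cut-off; under the assumptions above, 21% obese would become 37% to 51%. A case-control difference unrelated to adiposity is possible. Over the assumed fluid range, with no offset, it would be 0.4 to 1.6 kg/m², but its true size and net direction are unknown. Height, gain, fluid weight, the BMI distribution and the cut-off of 30 are all assumptions.

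The consequence is confined to the maternal group comparison, the maternal-offspring correlation and any use of obesity as a covariate. It would be wrong to infer that the main offspring result is compromised: the sample size rests on neonatal diastolic blood pressure, and the unadjusted comparison of offspring does not use maternal weight.

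**What to change.** At the interview already planned, extract from the antenatal record the earliest weight in this pregnancy, or a recorded pre-pregnancy weight, with the gestational age at weighing. Define maternal BMI on that weight, and state the cut-off if obesity is to be a category. If the questionnaire already records such a weight, it is enough to say that obesity is defined on it.

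Where only a weight from 20 weeks or later exists, including one taken at recruitment, flag it and repeat the analysis without those women. In cases such a weight has the same contamination, so it should not be treated as equivalent to an early one. Keep the week-30 weight to describe gestational weight gain.

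The cost is one extracted weight with its date or gestational age, and no extra visit or device. The downside is that some first weights will be missing or late, which leaves fewer women in the repeat analysis.

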## Introduction

Hypertension is an independent modifiable risk factor for the development of cardiovascular diseases (CVDs) (1). Although hypertension is prevalent in adults and increasingly becoming prevalent in children (1), there has been documented reports of hypertension in neonates (2). The Neonatal Intensive Care Unit (NICU) report showed that hypertension may occur in up to 3% of neonates (3) while a large multi-centre study by the Worldwide Acute Kidney Injury Epidemiology in Neonates (AWAKEN) reported a 1.8% incidence rate of neonatal hypertension (4). Although the origin and major predisposing factors for high blood pressure (BP) in neonates is unknown, studies have shown that acute kidney injury (4), maternal hypertension and pre-eclampsia (PE) may be responsible (5). PE is a hypertensive disorder defined as the presence of hypertension (BP ≥ 140/90 mm Hg) on two occasions at least 4 h apart with proteinuria or severe hypertension (BP ≥ 160/110 mm Hg) with or without proteinuria occurring after 20 weeks of gestation in a previously normotensive woman (6). PE is thought to be a contributor to neonatal hypertension and has been associated with small for gestational age babies with increased risk for CVDs (7).

As suggested by the concept of the Developmental Origins of Health and Disease, the maternal gestational environment may have a significant impact on foetal health with offspring been programmed for hypertension, obesity, diabetes, and CVDs in adulthood (8). Foeto-placental vascular endothelial dysfunction may cause epigenetic alteration in the intrauterine environment of the foetus and may be the origin of chronic diseases later in life (9). Moreover, PE has been reported to be associated with foeto-placental vascular endothelial dysfunction (10, 11). More so, there is evidence that children born to pre-eclamptic mothers have higher intima media thickness, adverse cardiac remodelling and higher blood pressure (12, 13) suggesting that offspring of pre-eclamptic mothers are prone to CVDs. However, all these studies were done in non-African populations and therefore may not necessarily apply to people of African ancestry.

In South Africa, PE affects about 5% of pregnant women and 12% of primigravidae (14, 15). Although the cause(s) of PE remain unclear, it is thought to stem from placental malfunction during pregnancy (16) resulting in foetal hypo-perfusion associated with oxidative stress and low-grade inflammation (17–19). Studies have shown an imbalance of antioxidants and reactive oxygen species (ROS)-generating enzymes in pre-eclamptic placentas with endothelial dysfunction (20, 21). Furthermore, placental hypoxia which is common in PE has been shown to be associated with maternal endothelial dysfunction (22). These findings suggest PE to be associated with endothelial dysfunction, a precursor of CVDs. This has been evident in pre-eclamptic subjects compared to normotensive controls (23, 24). It is therefore possible that exposure of the unborn child to this pro-CVD environment may program the offspring for greater susceptibility to hypertension and CVDs (25, 26). Although Meeme et al. showed endothelial dysfunction to be associated with PE in rural South African women (27), it is still unknown whether children born to these pre-eclamptic mothers are at greater risk of CVDs. Hence, this protocol is for a study aiming to assess CVD risk profile of neonates and infants exposed to PE *in-utero* and correlate them with markers of maternal cardiovascular risk, oxidative stress and endothelial function. The study will:

Assess maternal cardiovascular risk profile during pregnancyAssess cardiovascular risk profile of neonates at birthDetermine changes in cardiovascular risk profile from birth to 6 weeks after birthCorrelate the maternal and neonate CVD risk profile

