### Biomarker Assessments

Blood and cord blood sample will be collected from pregnant women and early morning mid-stream urine samples will be collected from their offspring by the research nurse. These samples will be used to measure oxidative stress markers [lipid peroxidation, total antioxidant capacity, and 8-hydoxyl-2-deoxyguanine (8-OHdG)], lipid profile markers (total cholesterol, triglycerides, LDL-cholesterol, and HDL-cholesterol), insulin resistance markers [fasting glucose, insuli, and glycated haemoglobin (HbA1c)], endothelial function markers [endocan, nitric oxide (NO), and asymmetric dimethyl arginine (ADMA)] and renal function markers [glomerular filtration rate (GFR), creatinine and albumin] (37, 38). Fasting glucose and insulin will be used to calculate the homeostatic model assessment of insulin resistance (HOMA-IR) while urinary albumin and creatinine will be used to calculate the albumin to creatinine ratio (ACR) (37, 38).

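### The tests named for objective 3 (change from birth to 6 weeks) do not link an infant's 6-week value to its own birth value, and blood-marker change within a group mixes specimen with age

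*Protocol article*

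**What the plan says.** The third of the four aims at the end of the Introduction is to determine "changes in cardiovascular risk profile from birth to 6 weeks after" birth. Study Design and Procedure supports this for the physical measures: weight, length, blood pressure and PWV at birth, then blood pressure, anthropometry and PWV again at 6 weeks.

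Statistical Analysis gives each named test a purpose:

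- The independent-sample t-test "will be used to compare mean differences between groups (pre-eclamptic and normotensive pregnant women and their offspring").
- MANOVA "will be used to compare continuous variables for two or more independent variables where necessary".
- Chi-square and Pearson correlation assess the relationship between "cardiometabolic risk factors and PE at baseline and follow-up for both mother and child".

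On specimens, Study Design and Procedure says for birth: "Cord blood will be collected for determination of cardiometabolic risk markers". For 6 weeks it says: "Then, blood and urine samples will be collected for the assessment of endothelial function" and other markers. Biomarker Assessments assigns blood and cord blood to the women and says that "early morning mid-stream urine samples will be collected from their offspring". It lists no infant blood and gives no visit for the urine.

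**The concern.** Change over time is a question about the same infant measured twice. A comparison of groups at birth and another at 6 weeks answers two different questions, one at each age. If one comparison is significant and the other is not, that does not show that the group difference changed. If both are significant, that does not show that it stayed the same. Nor does either comparison say how much infants in one group changed.

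The 6-week visit exists largely for this aim. Without a stated within-infant analysis, the natural way to write it up is to set the two cross-sections side by side and interpret their agreement or disagreement.

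Blood biomarkers have a second difficulty. The birth and 6-week specimens differ in kind, so a raw difference within a group reflects specimen as well as age.

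**Working it through.** **1. Objective against tests.**

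| Named test | What it compares | Uses the infant's own birth value? |
|---|---|---|
| Independent-sample t-test | PE group v normotensive group | Not stated |
| MANOVA, where needed | Continuous variables across independent variables; no visit factor named | Not stated |
| Chi-square, Pearson | Marker v PE, at baseline and at follow-up | No |

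No paired test, change score, repeated-measures factor or mixed model is named.

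**2. Does the sample size imply a change analysis?** No. Sample Size Calculation uses a single between-group DBP contrast: 42.11 − 30.17 = 11.94 mmHg. Pooled SD = √[(11.89² + 11.49²)/2] = 11.69. The stated 49 per group is reproduced approximately (47 to 50, depending on the SD and the formula) only with two-sided alpha 0.01 and 99% power, and the article states no power. Nothing in it concerns change from birth.

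**3. What a change analysis could detect (illustration).** Assumptions: DBP SD 11.69 at both visits, n = 49 per group, two-sided alpha 0.05, 80% power (multiplier 1.96 + 0.84 = 2.80). The birth-to-6-week correlation ρ is not in the documents and is varied.

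- SE of within-group change = 11.69 × √[2(1−ρ)/49]
- SE of between-group difference in change = 11.69 × √[4(1−ρ)/49]

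| ρ | SE, within group | Detectable within-group change (mmHg) | SE, between groups | Detectable difference in change (mmHg) |
|---|---|---|---|---|
| 0 | 2.36 | 6.6 | 3.34 | 9.4 |
| 0.3 | 1.98 | 5.5 | 2.79 | 7.8 |
| 0.5 | 1.67 | 4.7 | 2.36 | 6.6 |
| 0.7 | 1.29 | 3.6 | 1.83 | 5.1 |

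The planned number can therefore support a useful change analysis for DBP.

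**4. How often would two cross-sectional tests disagree when nothing has changed?** With the same true group difference at both visits, disagreement = 2 × [power − P(both significant)].

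- At an assumed 80% power and ρ = 0: 2 × (0.80 − 0.64) = 32%. At ρ = 0.3, 0.5 and 0.7 it is 27%, 23% and 17%.
- For DBP as sized (11.94 mmHg, SD 11.69, 49 per group, alpha 0.05), power is 99.9% and disagreement is about 0.2% at any ρ from 0 to 0.7.

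The larger figures could apply only to markers or effects with much lower power, for which the documents give no inputs.

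**5. Why adjusting for the birth value does not serve here.** Suppose the group difference is 11.94 mmHg at both visits, so there is no differential change. With equal SDs, ANCOVA of the 6-week value on the birth value has expected group effect 11.94 × (1−ρ): 8.4, 6.0 and 3.6 mmHg at ρ = 0.3, 0.5 and 0.7. Read as differential change, each would be false. The groups are not randomised, and birth blood pressure is itself an outcome of the exposure.

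**6. Specimens.** Let the cord-to-infant offset be *c*. Within-group change estimates (true change + *c*), and *c* cannot be separated from age. In the between-group difference in change, *c* cancels only if it is equal in both groups.

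**The case against.** The strongest reply is that the tests could be made to serve. The article does not say which variable enters the t-test. Applied to each infant's change, an independent t-test would answer the between-group part of the aim, and MANOVA can be run as repeated measures. An article may also leave the form of a model to a fuller document.

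Part of this stands. A reader might infer that the planned tests cannot answer the aim at all, and the documents do not support that. They also do not say that the authors will judge change by comparing significance across visits. That is a risk left open by the wording. But the article does name its tests and their purposes, none of them is change, and a t-test on change scores would still leave within-group change untested.

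A reader might also attach a large error rate to this. The 17% to 32% disagreement range rests on an assumed 80% power and does not apply to DBP as sized. Likewise, a charge that the plan overstates the standard error of change by treating visits as independent samples would fail, because the article proposes no test of birth against 6 weeks.

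On specimens, the difference between the two sections may be loose wording: Biomarker Assessments omits infant blood but does not rule it out. That urine is not taken at birth would be an inference from silence. The timeline figure is not shown in the text reviewed and may settle both points.

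**Conclusion.** The concern holds in limited form. One of the four stated aims has no stated analysis that links an infant's two measurements. Followed as written, the plan yields separate cross-sections. For blood pressure, PWV, weight and length the data are comparable across visits and only the analysis is missing. For blood biomarkers, within-group change also confounds specimen with age, and a between-group difference in change rests on an equal specimen offset in both groups.

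This conclusion follows from the text and needs no assumed correlation or power. The detectable differences shown are illustrations under stated assumptions. The disagreement rates are not a measure of this study's error. The statements on offspring samples differ between sections and need reconciling, but the documents do not establish which samples will in fact be taken. The change is worth making because it corrects a mismatch with a stated aim at almost no cost.

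**What to change.** 1. Add to Statistical Analysis, for SBP, DBP, PWV, weight and length, a mixed model with group, visit and group-by-visit and a within-infant covariance. Take objective 3 from the visit terms (change within each group) and the interaction (difference in change). With complete pairs, paired within-group estimates plus a t-test on per-infant change scores are equivalent. With the 20% loss that the article allows for, the mixed model also uses infants seen only at birth.
2. Do not use ANCOVA on the birth value for this aim.
3. For blood biomarkers, compare groups at birth and at 6 weeks separately and do not report within-group change. If a between-group difference in change is reported, state that it assumes the same cord-to-infant offset in both groups.
4. Reconcile Biomarker Assessments with Study Design and Procedure on whether infants give blood at 6 weeks, and state whether urine is collected at birth. If it is not, the urinary albumin-to-creatinine ratio has no birth value and no change to report.

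Cost: a few sentences of analysis and specimen wording, and within-group biomarker change is lost as a reported result. No extra visits or participants are needed.
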